### Outcome measures

In cost-effectiveness studies, costs are linked to treatment or clinical outcomes. All outcomes will be assessed at all three measurement moments.

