### Statistical analysis

First, descriptive statistics will be performed to describe the demographic characteristics of the study population.

Second, primary measures of effect will be analysed using within group comparisons (pre-post treatment) and between group comparisons. The latter one will use difference scores (pre-post intervention) after which the treatment effects of the two treatment conditions will be compared. Statistical testing will be done using either the paired t-test or the Wilcoxon signed-rank test for comparisons within the treatment groups and the unpaired t-test or the Mann–Whitney U test for comparisons between the treatment groups.

Third we will describe the mean costs per respondent in both treatment groups. Differences in costs between the intervention group and the control group will presented based on the trial data, and 95% confidence intervals will computed based on bootstrap re-sampling with 5000 replications of the trial data. Separate estimates will be made for different cost categories. For the cost-effectiveness analysis, mean annual societal costs will be linked to the primary measure of effect (Aggressive behaviour and Delinquent behaviour). A cost utility analysis will link the EQ-5d based utilities to the cost.

Fourth, point estimates for the incremental cost-effectiveness and cost utility ratio (ICER) will be computed on complete cost-effect pairs by dividing the incremental societal costs by the incremental effects at 12 months. Uncertainty around the ICERs will be estimated using bootstrapping, generating 5000 replications of the original dataset. A cost-effectiveness acceptability curve (CEAC) will be generated to represent the probability that MST is cost-effective compared to usual care over a range of thresholds [26,36].

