### Strengths and limitations

This study will contribute to the extension of scientific knowledge about economic evaluation in the field of child and youth care. This concerns the evaluation of the actual balance between costs and effects in a field of care where this has hardly ever been explored before, i.e. with very limited sources to derive costs of other outcome valuations from. The study will be conducted as part of a randomized controlled trial. By using such a design, it can be assumed that any confounding variables are cancelled out.

Furthermore, the study will be conducted as a multicentre trial. This will increase the generalizability of the study because this will lead to a large number of participants, different geographic locations and the ability to compare results among organizations. We will obtain both direct and indirect costs across the entire field of youth care. We will also include quality of life measures. To increase inclusion and prevent loss to follow up, all adolescents and parents will receive assistance in administering the questionnaires. Finally, most outcome variables will be assessed via two informants. Multi-informant assessment is recommended as a way to obtain a more complete picture of the adolescent than reliance on self- or parent-report alone [16].

Despite the strengths and innovative aspects of this cost-effectiveness study, there are some issues that our study is unable to take into account. First, follow-up is limited to a period of six months. To determine long-term effects of the intervention, there should be follow-up after a couple of years to assess the effects and costs when the adolescent is older. Second, it is to be expected that we will be dealing with a ‘difficult-to-reach”-population.

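### The cost difference, the cost-utility ICER and its CEAC are described without T1 adjustment, although T1 utility and, by inference, T1 resource use are collected: valid, but less precise than the data allow

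*Protocol article*

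**What the plan says.** The Statistical analysis section of the protocol article sets out the economic estimators in order.

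- Costs: "Third we will describe the mean costs per respondent in both treatment groups". The difference between arms is reported, and "95% confidence intervals will computed based on bootstrap re-sampling with 5000 replications of the trial data".
- ICERs: "computed on complete cost-effect pairs by dividing the incremental societal costs by the incremental effects at 12 months". Then: "Uncertainty around the ICERs will be estimated using bootstrapping, generating 5000 replications of the original dataset". A CEAC follows.
- Cost-utility: costs are linked to EQ-5D utilities, with no mention of T1.
- Behavioural effect: for the between-group comparison of the primary measures, "The latter one will use difference scores (pre-post intervention) after which the treatment effects of the two treatment conditions will be compared". The cost-effectiveness analysis uses aggressive and delinquent behaviour as its effect, but does not say whether the difference scores are what enters the ICER.

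On the availability of T1 data, the Outcome measures section states: "All outcomes will be assessed at all three measurement moments". The Abstract lists the TiC-P and EQ-5D and places the first data collection before treatment, and the Data collection procedure section gives the questionnaires at T1. T1 utility is therefore available. T1 resource use follows by inference from these places and the Costs items section, which names the TiC-P but gives no recall period.

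The Strengths and limitations section says of the randomised design that "it can be assumed that any confounding variables are cancelled out".

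**The concern.** The economic result is the stated aim of this article. T1 utility is likely to predict later utility, and T1 care use may predict later care cost. Randomisation balances these on average, not in the single sample obtained. An estimator that ignores T1 carries part of whatever gap occurred into the increments. Resampling the observed data does not remove a gap already in them.

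If the true utility difference is small, a chance T1 gap could influence the sign of the incremental utility, and with it the ICER quadrant and the height of the CEAC. A T1 cost gap acts in the same way on the numerator. The plan is also uneven: it uses T1, by subtraction, for the behavioural comparison, and describes no use of it for costs or utility.

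**Working it through.** **Inputs from the article.** Target of 100 per arm (Abstract; Sample size), 1:1 allocation run separately by site (Randomization), 5000 bootstrap replications (Statistical analysis).

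**Assumed, because the article gives none.** Correlation rho between T1 value and outcome of 0.2 to 0.7; equal SD at T1 and follow-up; where a utility scale is needed, an SD of 0.20 to 0.30.

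**The plan's own figure.** The article gives no precision figure for the economic analysis. Its first sample-size figure reproduces: for a medium effect (d = 0.5), two-sided alpha 0.05 and power 0.80, the normal approximation gives 63 and the t-test 63.8, hence 64 per group. That figure sizes a test of outcomes and is not used below.

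**Formulae, in SD units.**

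- SE of an unadjusted difference: sqrt(2/n) = sqrt(2/100) = 0.141.
- SE adjusted for T1: sqrt(2/n) × sqrt(1 − rho²).
- SE of a change-score difference: sqrt(2/n) × sqrt(2(1 − rho)).
- 95% range of the chance T1 gap: ±1.96 × 0.1414 = ±0.277.
- Expected carry-over per unit of T1 gap: rho (unadjusted), 0 (adjusted), −(1 − rho) (change score).

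| rho | SE unadjusted | SE adjusted | Interval narrower by | SE change score | Shift from a gap of +0.277: unadjusted | Same: change score |
|---|---|---|---|---|---|---|
| 0.2 | 0.141 | 0.139 | 2% | 0.179 | +0.055 | −0.222 |
| 0.3 | 0.141 | 0.135 | 4.6% | 0.167 | +0.083 | −0.194 |
| 0.5 | 0.141 | 0.122 | 13% | 0.141 | +0.139 | −0.139 |
| 0.7 | 0.141 | 0.101 | 29% | 0.110 | +0.194 | −0.083 |

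The percentage narrowing does not depend on n. In equivalent sample size, n/(1 − rho²), adjustment at 100 per arm is worth 110, 133 or 196 per arm at rho 0.3, 0.5 or 0.7.

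**On the utility scale.** With an SD of 0.20 to 0.30, the SE of the T1 gap is 0.1414 × 0.20 = 0.028 to 0.1414 × 0.30 = 0.042. At rho = 0.5, half of any gap is expected to reappear in an unadjusted follow-up difference.

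**Check by simulation** (8000 trials of 100 per arm, no true effect). At rho 0.3, 0.5 and 0.7 the slope of the estimate on the T1 gap was 0.30, 0.50 and 0.71 unadjusted, about 0 adjusted, and −0.70, −0.50 and −0.29 for change scores. The mean of the unadjusted and of the adjusted estimates stayed within about 0.003 of zero: neither is biased over repeated trials.

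**What this means for the behavioural ICER.** If its denominator is the pre-post difference, T1 is already used but over-corrected. Below rho = 0.5 the change score is also less precise than the unadjusted follow-up difference (SE ratio 1.18 at rho = 0.3).

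**The case against.** The case against has real weight.

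- **The planned method is valid.** Under randomisation the unadjusted increments are unbiased, and the bootstrap interval already reflects sampling variation, chance imbalance included. This stands: the issue is precision and dependence on the gap that occurred.
- **Silence is not a choice.** Dividing incremental cost by incremental effect defines an ICER and would remain true with adjusted increments; covariates are often left to an analysis plan. This stands in part. The article does not exclude adjustment, but it spells out each estimator, and as described they are unadjusted for cost and utility.
- **The gain for costs may be small.** The correlation is unknown and the TiC-P recall period is not given. At rho of 0.2 to 0.3 the narrowing is only 2% to 4.6%. This stands as a limit on size.
- **T1 is not a clean baseline everywhere.** In the North, the Recruitment section puts randomisation after the residential period and the first questionnaire at a later appointment before treatment. T1 there is self-reported after allocation and could be coloured by it. This stands as a downside to state, but does not defeat adjustment.

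A reader might also infer that the Strengths and limitations section gives the reason for omitting adjustment. It does not: it is a general remark on randomised designs and mentions neither adjustment nor costs nor utility. It is nevertheless worded too strongly for a single trial.

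**Conclusion.** The point holds for the cost difference, the cost-utility ICER and its CEAC: the described increments leave out T1 information that the trial collects (for costs, by inference). At assumed rho of 0.3, 0.5 or 0.7, adjustment would narrow the intervals of the increments by about 5%, 13% or 29% and remove the expected carry-over of a chance T1 gap. For costs the gain may be only a few per cent. It is a worthwhile improvement to the headline analysis and does not invalidate the plan.

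Three stronger readings are tempting and not supported. First, that both ICERs rest on raw arm means: the behavioural one may use the difference scores, and the text leaves this open. Second, that a T1 gap passes in full into the result or biases it: the fraction is rho (or −(1 − rho) for change scores), and the expected bias is zero. Third, that the gain can be read as power at d = 0.5: that effect size belongs to the outcome test, and the Sample size section itself says no formal power calculation can be presented for the economic comparison.

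**What to change.** In the Statistical analysis section:

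1. Estimate incremental cost, incremental EQ-5D utility and the incremental CBCL/YSR effect from regressions on arm, the corresponding T1 value and site (randomisation is run separately by site).
2. Refit these models within each of the 5000 bootstrap replications, resampling cost-effect pairs within arm.
3. Build the cost interval, the ICERs and the CEAC from the adjusted increments. This also settles which behavioural effect enters the ICER.
4. Keep the unadjusted differences as description, and report the unadjusted economic result as a sensitivity analysis.

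In Strengths and limitations, say that randomisation balances confounders on average.

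The cost is a few sentences and a few lines of code in the bootstrap loop. Three downsides should be stated: the adjusted increments will not equal the differences of the tabulated means; the gain for costs depends on an unknown T1 correlation and recall period; and T1 in the North is self-reported after allocation, though before treatment, which is why the unadjusted sensitivity analysis is needed.

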## Discussion

This paper presents the design of a randomized controlled trial to investigate the cost-effectiveness of MST in the Netherlands, an intervention program for families and youth with severe psychosocial and behavioural problems.

Studying the cost-effectiveness of this intervention is important in order to provide information to policy makers on whether the provision of this intervention represents good value for money. Introducing a cost-effective evidence based program will result in substantial health gains at acceptable costs. MST can be easily embedded in both usual mental health care and welfare services in The Netherlands.

### Strengths and limitations

This study will contribute to the extension of scientific knowledge about economic evaluation in the field of child and youth care. This concerns the evaluation of the actual balance between costs and effects in a field of care where this has hardly ever been explored before, i.e. with very limited sources to derive costs of other outcome valuations from. The study will be conducted as part of a randomized controlled trial. By using such a design, it can be assumed that any confounding variables are cancelled out.

Furthermore, the study will be conducted as a multicentre trial. This will increase the generalizability of the study because this will lead to a large number of participants, different geographic locations and the ability to compare results among organizations. We will obtain both direct and indirect costs across the entire field of youth care. We will also include quality of life measures. To increase inclusion and prevent loss to follow up, all adolescents and parents will receive assistance in administering the questionnaires. Finally, most outcome variables will be assessed via two informants. Multi-informant assessment is recommended as a way to obtain a more complete picture of the adolescent than reliance on self- or parent-report alone [16].

Despite the strengths and innovative aspects of this cost-effectiveness study, there are some issues that our study is unable to take into account. First, follow-up is limited to a period of six months. To determine long-term effects of the intervention, there should be follow-up after a couple of years to assess the effects and costs when the adolescent is older. Second, it is to be expected that we will be dealing with a ‘difficult-to-reach”-population.

## Conclusions

Cost-effectiveness is a research topic that has hardly been looked at in the child and youth care field, both internationally and nationally [37-40]. More knowledge about cost-effectiveness in child and youth care will aid policy makers, health care authorities as well as judicial authorities, to set priorities and decide on implementation of treatment modalities for youth with serious behavioural disturbances. This study can provide information on both the feasibility of CEA in this field in general, and on the cost-effectiveness of MST specifically.
